### Outcomes

Primary and secondary outcomes will be assessed three times (see Fig. 2 for an overview of outcomes and data time points). Unless they request it, participants will not be physically seen by the psychologists during follow-ups. They will be asked by email 1 month (T1) and 6 months (T6) after the inclusion visit to answer the online questionnaires again and, if they accept, to validate the sending of their alcohol consumption data and, for the participants of the experimental condition, the sending of their MBM data through the mobile application. The participant code included in the file will allow the scientific team to associate the new data with the previous data of this specific participant.

### Statistical considerations

#### Power analysis

At an alpha risk of .05, the number of 120 subjects in total is sufficient to obtain a power greater than .80. This estimate is derived from a 3000 iteration Monte Carlo simulation based on a baseline of real data collected in November 2021 (*N* = 1917) with a Gamma distribution. In this simulation are parameterized an average decrease of 10% of the BD score in control group and an average decrease of 20% for the experimental group with an intra-subject variability (SD) linearly depending on the individual baseline (estimated to be ¼ of the baseline value + 0.5).

Considering a potential attrition rate of approximately 30%, 170 subjects will be included in the study at T0.

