### Study design and setting

All the study design and setting (see SPIRIT Checks in Additionnal File 1) has been elaborated by the trial steering committee (TSC) which is made up of the research team who authored this article, with the exception of Messrs [name] and [name], who were respectively responsible for the development and design of the ALCOODUC mobile app. The TSC, comprising nine people, is made up of academics specializing in prevention issues and field experts specializing in alcohol-related problems and/or the practice of mindfulness meditation. This steering committee met on a monthly basis during the protocol design phase and validated each stage of the protocol submission process, notably at the level of the national ethics committee (see the “Ethics approval and consent to participate” section for a brief description of the French system).

This is a randomized controlled study in parallel groups. It will compare the monthly BD score between the control group and the experimental group, and the allocation ratio is 1:1.

One hundred seventy volunteer participants from the University of Caen (France) will be included in this research protocol (see Fig. 1). During the initial visit, after presentation of the study and signature of the consent form presented by one of the two psychologists in charge of the interviews, all participants will complete various online questionnaires (estimated completion time 40 min; LimeSurvey) as well as a screening for neuropsychological impairments using the BEARNI tool (Brief Evaluation of Alcohol-Related Neuropsychological Impairments [33]; estimated completion time of 20 min). Eighty-five participants will benefit from the control condition (i.e., a motivational interview), and 85 other participants will benefit from the experimental condition (i.e., a motivational interview associated with a mindfulness meditation session and intention implementation; estimated duration 1 h).

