### Eligibility criteria

To be eligible, subjects must meet all the defined inclusion criteria. The population, made up of students who consume alcohol recruited within the University of Caen, will be aged between 18 and 30 years, French native speaker, of both sexes, with a binge drinking score^2^ > 1, having signed an informed consent. In addition, subjects meeting any of the following exclusion criteria will not be eligible to participate in the research: pregnant or breastfeeding students, students reporting a history of neurological, neurosurgical, psychiatric or endocrine disease, or infectious disease.

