A second step will consist in conducting the main analyses. Recall that by “five dependent variables (DVs),” we mean here binge drinking score (BD), weekly alcohol consumption (WAC), craving, impulsivity, and readiness to change (RC). Prior to the main analyses, we will check whether there is a significant relationship between age and the baseline scores of any of the five DVs. We expect the age range to be rather small apart from potential serious outliers, in a sample that is not particularly large, and we do not expect age to play a noticeable role on most of the DVs, except for BD scores where it is suspected that binge drinking behaviors are most common in the younger population. For these reasons, we want to avoid adding age as a covariate unless the data show that we really have to. We will conduct five similar general linear analyses, with the following variables: dependent variable: evolution scores (T0 → T1) of one of the five DVs; factors: condition, sex, condition*sex; covariates: AUDIT score, baseline of the DV at hand. Covariate(s) that will be added if either they are significantly related to the baseline scores of the DV at hand, or the two groups were not matched at T0 with respect to them: age, trait anxiety level, depression level. We add as a covariate the baseline of the DV at hand because we expect that the higher level of self-consciousness brought by the very fact of taking part in this demanding study might trigger an effect of regression to the mean, by which people with a larger baseline score (and hence a larger margin for improvement) would show better results no matter in what condition they were placed.

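### The stated power above .80 with 120 subjects does not follow from the protocol's own simulation inputs, which allow at most about 58% two-sided or 70% one-sided

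*Protocol article*

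**What the plan says.** The Power analysis section gives the claim and its inputs together: "At an alpha risk of .05, the number of 120 subjects in total is sufficient to obtain a power greater than .80". The figure comes from a 3000-iteration Monte Carlo simulation "based on a baseline of real data collected in November 2021 (*N* = 1917) with a Gamma distribution". The effect is "an average decrease of 10% of the BD score in control group and an average decrease of 20% for the experimental group". The intra-subject SD depends linearly on the individual baseline and is "estimated to be ¼ of the baseline value + 0.5". To allow for about 30% attrition, 170 are enrolled.

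Elsewhere, Study design and setting says "the allocation ratio is 1:1", so 120 analysed means 60 per arm. The eligibility criteria admit students "with a binge drinking score^2^ > 1". The Data management and analysis plan section describes the primary analysis: "We will conduct five similar general linear analyses, with the following variables". The dependent variable is the T0 to T1 change. The factors are condition, sex and their interaction, and the covariates are AUDIT score and the baseline of the outcome. Condition is coded 1/0; the coding of sex is not stated. The Interventions section frames the trial as a superiority comparison of the two arms.

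The article does not give the Gamma mean and shape, the sidedness of the test, or the test used in the simulation.

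**The concern.** A difference of 10% of baseline is set against an SD of at least 25% of baseline. That is a standardised effect of at most 0.40, and 60 per arm is too few to detect 0.40 with 80% power. The conflict lies within one paragraph, so neither the undisclosed Gamma parameters nor a fuller analysis plan would remove it on the natural reading of the SD.

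The sample size rests on this figure: 170 is 120 inflated for attrition, and the design section relies on that inflation for adequate power and does not replace participants who leave. If the power is overstated, readers will take the trial to be more informative about the planned effect than it is.

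**Working it through.** **Inputs (protocol article).** Alpha .05; 120 in total at 1:1, so n = 60 per arm; expected T1 score 0.90B (control) and 0.80B (experimental), where B is the baseline BD score; SD = 0.25B + 0.5. *Assumption:* this is the SD of T1, or of the change, around its expected value given B.

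**Attrition step.** 170 × 0.70 = 119, and 120/0.70 = 171.4. This step is sound; the trouble is in the 120.

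**Attempt to reproduce the stated power: upper bound.** Let m be the mean of B. A linear model on change estimates an average arm difference of 0.10m. The average residual variance is at least E[(0.25B + 0.5)²], which by Jensen's inequality is at least (0.25m + 0.5)². Hence

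d ≤ 0.10m / (0.25m + 0.5) < 0.10/0.25 = 0.40

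for every baseline distribution. At the unreachable limit d = 0.40, with noncentrality d√(n/2):

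| Analysed | Noncentrality | Two-sided power | One-sided power |
|---|---|---|---|
| 60 per arm | 0.40 × √30 = 2.191 | 58.4% | 70.3% |
| 85 per arm (all 170, no attrition) | 0.40 × √42.5 = 2.608 | 73.7% | 83.0% |
| 99 per arm | 0.40 × √49.5 = 2.814 | 79.97% | – |
| 100 per arm | 0.40 × √50 = 2.828 | 80.4% | – |

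Even at the limit, 80% two-sided power needs about 200 analysed.

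**Effect of baseline spread (Gamma parameters assumed).** For a Gamma baseline with mean m and shape k, Var(B) = m²/k and

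E[(0.25B + 0.5)²] = 0.0625(m² + m²/k) + 0.25m + 0.25.

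Fitting one common baseline slope when the two arms' slopes differ by 0.10 adds 0.05² × m²/k. Then d = 0.10m divided by the square root of the sum.

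| m | k | Sum | d | Power, 60 per arm, two-sided |
|---|---|---|---|---|
| 10 | 1 | 15.25 + 0.25 = 15.50 | 0.254 | 28% |
| 20 | 1 | 55.25 + 1.00 = 56.25 | 0.267 | 31% |
| 20 | 2 | 42.75 + 0.50 = 43.25 | 0.304 | 38% |
| 20 | 5 | 35.25 + 0.20 = 35.45 | 0.336 | 45% |
| 20 | no spread | 30.25 | 0.364 | 51% |
| 40 | 5 | 130.25 + 0.80 = 131.05 | 0.349 | 48% |

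**Simulation.** Runs of 3000 iterations with baseline truncated above 1 agree. For change adjusted for baseline, two-sided, power was 32 to 48% over means 10 to 40 and shapes 1 to 5. A very tight baseline (shape 50, mean 40) gave 54%.

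**Other analyses at N = 120.** Percent change and baseline-weighted models gave 34 to 55% two-sided. A log ratio with Gamma errors gave at most 59% two-sided and 70% one-sided. With condition × sex in the model and sex also dummy-coded, the condition coefficient refers to one sex only and had 16 to 32%; with sum-coded sex it had about the same power as the model without the interaction. AUDIT was not simulated, because the article gives no correlation for it. No between-arm analysis at N = 120 reached .80.

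**Where .80 does appear.** It appears for 120 *per arm* with a tight baseline (80 to 83%, but 58 to 66% at shapes 1 to 2), and for the within-group change in the experimental arm (about 97 to 100%). Neither is what the article states.

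**Detectable difference.** At 60 per arm, 80% two-sided power needs d = 0.516. At the limit this is 0.516 × 0.25 = 12.9 percentage points. Ignoring the small slope term, it is 0.516 × √130.25/40 = 14.7 points for m = 40, k = 5, and 0.516 × √15.25/10 = 20.1 points for m = 10, k = 1.

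**The case against.** The strongest objection concerns the SD. The article calls it intra-subject variability without saying whether it belongs to the change or to a single measurement. Study objectives and Study design and setting say that the monthly BD score is followed by repeated momentary questionnaires. If the SD were per measurement and the one-month score averaged three independent ones, power at mean 20 and shape 2 would be about 82% (two: about 65%). So a reader might infer that power above .80 is strictly impossible, and that goes too far. But the Power analysis section mentions no averaging, and Binge drinking practices defines a single T1 score from three items. The point stands on the natural reading, and the ambiguity is itself something to settle.

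Other stronger readings are also not supported:

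- *58% as the ceiling without qualification.* Sidedness is not stated; the one-sided ceiling is 70%. All 170 analysed one-sided would pass 80% at the limit (83%), but the claim is made for 120.
- *A power of 30 to 50% as fact.* This rests on assumed Gamma parameters and on a model without the sex interaction. Only the ceiling is free of the Gamma assumption.
- *The trial will more likely than not miss its target effect.* That follows under the assumed Gamma shapes, but not from a ceiling above 50%.
- *A non-significant result will be reported as no added value.* The article nowhere says so.

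It is also true that the error biases neither the effect estimate nor the type I error.

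**Conclusion.** The statement is wrong as written. On the protocol's own effect and SD, 120 analysed subjects give at most about 58% power two-sided or 70% one-sided for the comparison of arms, against a claim above 80%. This bound needs no knowledge of the baseline distribution. It rests on the SD being that of the T1 score or change given baseline, and on a linear model for the change. With assumed Gamma means of 10 to 40 and shapes of 1 to 5, two-sided power is roughly 30 to 50%, and lower for the condition coefficient if sex is dummy-coded with the interaction. The simulation code is not shown, so the source of the discrepancy cannot be identified; a per-arm count or a within-group test are possibilities only.

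**What to change.** Re-run the simulation with the model planned in Data management and analysis plan: change on condition, sex, condition × sex, AUDIT and baseline. State with it:

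- whether the test is one- or two-sided;
- how sex is coded, and so what the condition coefficient estimates;
- what the SD refers to (one measurement, the T1 score, or the change);
- the Gamma mean and shape fitted to the November 2021 data.

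Replace the claim of power above .80 with the power obtained for 10% versus 20% at about 119 to 120 completers, and add the difference detectable at 80% power.

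The cost is one re-run and a change of wording. No additional participants are needed, and with 98 of 170 recruited at the time of the article (Trial status) the correction could be made before analysis. The stated power becomes less favourable.

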#### Data management and analysis plan

Missing data will exclude the corresponding participant from the analysis.

All models will be tested using R software and the expected level of statistical significance is .05. The statistical analyses will be conducted in two main stages and an additional exploratory stage. All details of the Statistical Analysis Plan (SAP) are included in a supplementary file available online (https://osf.io/3n4c6/files/osfstorage ).

A first step will consist in checking that the experimental and control groups are matched at T0. We will use *χ*^2^ tests of independence and Student *t*-tests to check that the randomization did result in two groups that were initially matched in terms of age, sex, AUDIT score, trait anxiety level, and depression level. Should this not be the case, the culprit variables will be controlled as additional factors/covariates in all subsequent analyses (although sex and AUDIT score will be part of the model in any case).

A second step will consist in conducting the main analyses. Recall that by “five dependent variables (DVs),” we mean here binge drinking score (BD), weekly alcohol consumption (WAC), craving, impulsivity, and readiness to change (RC). Prior to the main analyses, we will check whether there is a significant relationship between age and the baseline scores of any of the five DVs. We expect the age range to be rather small apart from potential serious outliers, in a sample that is not particularly large, and we do not expect age to play a noticeable role on most of the DVs, except for BD scores where it is suspected that binge drinking behaviors are most common in the younger population. For these reasons, we want to avoid adding age as a covariate unless the data show that we really have to. We will conduct five similar general linear analyses, with the following variables: dependent variable: evolution scores (T0 → T1) of one of the five DVs; factors: condition, sex, condition*sex; covariates: AUDIT score, baseline of the DV at hand. Covariate(s) that will be added if either they are significantly related to the baseline scores of the DV at hand, or the two groups were not matched at T0 with respect to them: age, trait anxiety level, depression level. We add as a covariate the baseline of the DV at hand because we expect that the higher level of self-consciousness brought by the very fact of taking part in this demanding study might trigger an effect of regression to the mean, by which people with a larger baseline score (and hence a larger margin for improvement) would show better results no matter in what condition they were placed.

In the main analysis, the use of evolution scores as a DV has a number of consequences. First, the effect of condition as reported in the analysis can actually be interpreted as an interaction effect between condition and the within-subject time factor. Second, the condition factor will be dummy-coded (experimental = 1; control = 0) so that the intercept of the model corresponds to the average evolution in the control group, in other words the effect of motivational interviewing alone (plus the fact of having to report your data on a daily basis), while the condition effect will correspond to the added value of the mindfulness training. We will investigate the simple effects of condition and sex, should their interaction turn out to be significant. All these analyses will be repeated using the evolution scores T0 → T6 as well.

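### Age, trait anxiety and depression enter the main models only through significance tests on T0 data, which leaves the models unfixed and may cost precision, though it does not bias the treatment effect

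*Protocol article*

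**What the plan says.** The section on data management and analysis plan in the protocol article has two stages.

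- **Balance check.** Chi-square and t-tests compare the arms at T0 on age, sex, AUDIT, trait anxiety and depression. If the arms differ: "Should this not be the case, the culprit variables will be controlled as additional factors/covariates in all subsequent analyses". Sex and AUDIT stay in the model whatever the test shows.
- **Main models.** Each of five outcomes (binge drinking score, weekly consumption, craving, impulsivity, readiness to change) is analysed as a T0 to T1 change score. Condition, sex, their interaction, AUDIT and the baseline of that outcome are always in. Age, trait anxiety and depression are optional: "Covariate(s) that will be added if either they are significantly related to the baseline scores of the DV at hand", or if the arms were not matched on them at T0.

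For age the article gives its reasons: a narrow age range, a modest sample, and no expected role except for binge drinking. It concludes that "we want to avoid adding age as a covariate unless the data show that we really have to". The level for all models is fixed: "the expected level of statistical significance is .05".

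**The concern.** Neither trigger asks the question that decides whether a covariate is worth including, namely whether it predicts the change score once the baseline of that outcome is in the model.

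- **Balance trigger.** Under Study design and setting, the article places allocation after all T0 measures. If allocation is sound, any T0 difference between the randomised arms is chance. A significant result then identifies a chance imbalance and not a prognostic variable. The article gives the test no other use, such as an audit of the envelope procedure; its only consequence is adjustment.
- **Baseline-association trigger.** This test has a genuine null but the wrong target. A variable related to the baseline outcome is favoured although the model already carries that baseline. A variable that predicts change but is unrelated to baseline is passed over.

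At stake are a main model that cannot be written down before the data are seen, and precision that covariates already collected could have supplied.

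**Working it through.** **Inputs.** From the article: level .05 (two-sided assumed), 120 analysed, 170 enrolled, 1:1 allocation, three optional covariates. The article does not give the correlations of those covariates with baseline or change, so a range is assumed below.

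**The plan's own figures.** Attrition: 120/(1 − 0.30) = 171.4, so 172 against the stated 170; in reverse, 170 × 0.70 = 119. These agree. Power: the article says "At an alpha risk of .05, the number of 120 subjects in total is sufficient to obtain a power greater than .80". With "an average decrease of 10% of the BD score in control group and an average decrease of 20% for the experimental group" and an SD "estimated to be ¼ of the baseline value + 0.5", the standardised difference stays below 0.10/0.25 = 0.40, and 60 per arm then gives at most 0.59 two-sided (0.71 one-sided). The stated power is therefore not reproduced if the formula is an SD. Read as a variance, it gives 0.89 at a baseline of 10 but 0.54 at a baseline of 5. The Gamma parameters and the simulated test are not printed. This is a separate matter, and nothing below depends on it; 80% power at 120 is simply taken as the benchmark.

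**Step 1: chance flags.** For the three optional covariates, 1 − 0.95³ = 1 − 0.857 = 0.143. Simulation gave 13.6% to 14.7%.

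**Step 2: what the second trigger selects.** With 120 participants, simulation gave these selection rates per covariate:
- prognostic but unrelated to baseline: about 5%;
- correlated 0.3 with baseline and useless once baseline is in the model: about 92%.

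**Step 3: cost of always including all three.** The fixed part of the model uses 6 parameters, leaving 120 − 6 = 114 residual degrees of freedom, or 111 with three more. The variance of the condition effect rises by about 114/111 = 1.027. From a benchmark of 0.80, power becomes 0.789 if the three explain nothing. It is 0.810, 0.830 and 0.871 if they explain 5%, 10% and 20% of residual variance. Break-even is 1 − 111/114 = 2.6%.

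**Step 4: the plan's two rules combined against a fixed set.** Simulated power, 6,000 trials per setting, n = 120, effect 0.52 residual SDs. With a coefficient of 0.3 for each covariate, the share of residual variance explained is 3 × 0.09/(1 + 0.27) = 21%; with 0.5, it is 3 × 0.25/(1 + 0.75) = 43%.

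| Assumed covariates | Plan's rule | Always included |
|---|---|---|
| Useless, unrelated to baseline | 0.795 | 0.786 |
| Useless, r = 0.3 with baseline | 0.788 | 0.787 |
| Prognostic (21%), unrelated to baseline | 0.708 | 0.787 |
| Prognostic (43%), unrelated to baseline | 0.570 | 0.785 |
| Prognostic (coefficient 0.3), r = 0.3 with baseline | 0.788 | 0.793 |

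A separate simulation of 4,000 trials per setting gave 0.806 against 0.794 (useless), 0.713 against 0.794 (prognostic, unrelated) and 0.780 against 0.786 (prognostic, r = 0.3).

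**Step 5: bias and type I error.** Under the plan's rule the mean estimate was within 0.004 of the truth in every setting. Type I error ran from 0.042 to 0.054 in the first simulation and from 0.044 to 0.052 in the second. The Monte Carlo standard error at 6,000 trials is √(0.05 × 0.95/6000) = 0.003, and where the rule gave 0.054 the fixed set gave 0.055. The low values (0.042 and 0.045) occur where the covariates are prognostic and unrelated to baseline; the fixed set stayed at 0.050 to 0.051 there. The rule is mildly conservative in those settings and nowhere liberal.

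**The case against.** The best defence is that this is a pre-stated algorithm using only T0 data. Neither trigger looks at follow-up outcomes or the treatment effect, so it is not outcome-driven model shopping. The covariates most likely to matter are already fixed. The article reasons about age, and the 18 to 30 range in the eligibility criteria supports it. Different covariates for different outcomes are not in themselves an error. The loss in Step 4 needs covariates that are strongly prognostic yet unrelated to baseline; when they are useless the plan's rule is slightly ahead, and when they are also correlated with baseline it nearly matches the fixed set.

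Most of this stands, and it limits the size of the point. It also rules out several stronger readings that a reader might infer:

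- **Inflated false positives or a biased estimate.** Not supported: Step 5 shows neither.
- **A 22.6% chance of a spurious culprit (1 − 0.95⁵).** This counts sex and AUDIT, whose tests cannot change the model. The relevant figure is 14.3%.
- **Both triggers test a null that is true by design.** That holds only for the balance tests.
- **Useless covariates do harm.** A fixed set may carry them too, at about one power point.
- **A fixed set is free.** It is cheap, not free.

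What the defence does not rescue is the choice of target. Expert knowledge about age is a reason to decide on age beforehand, outcome by outcome, and not to hand the decision to a test of something else. Nor is this a detail left to the unseen analysis plan: the article states both triggers as decision rules.

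**Conclusion.** The point holds as one of precision and pre-specification, limited to three covariates. After sound randomisation the balance trigger adds at least one of them by chance in about 14% of trials, treating the tests as independent. The second trigger selects on association with a baseline the model already contains. The treatment estimate remains unbiased and type I error is not inflated.

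The cost is a main model that is unknown until the T0 data are tested and can differ between outcomes, slightly conservative inference in some settings, and a possible loss of power. That loss depends on correlations the article does not give. Under assumed values it runs from none to about 8 points (0.708 against 0.787) when the three covariates explain about 21% of residual variance and are unrelated to baseline. It would be larger only for covariates stronger than that.

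**What to change.** - Delete both triggers.
- Name the covariates of each outcome's model in advance. The preferred set is the baseline of that outcome, AUDIT, sex, age, trait anxiety and depression, always included. If the team judges that age matters only for binge drinking, a pre-stated set per outcome also answers the point.
- Use the same sets for the T0 to T6 models.
- Report baseline characteristics by arm descriptively, without significance tests.

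The change is to wording only, since all three covariates are already collected at T0, and it should be made before follow-up outcomes are analysed by arm. It costs 3 of 114 residual degrees of freedom, about one power point at worst if the covariates are not prognostic, and it pays for itself once they explain more than about 2.6% of residual variance.

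### The BD model assumes one error variance although the power section lets the SD grow with baseline; if the sexes differ in baseline BD, its standard errors are wrong and HC3 would correct them

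*Protocol article*

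**What the plan says.** The power analysis section describes how the sponsor expects the BD score to behave. The simulation was "based on a baseline of real data collected in November 2021 (*N* = 1917) with a Gamma distribution". It sets "an average decrease of 10% of the BD score in control group and an average decrease of 20% for the experimental group". The spread around these means is then described as "an intra-subject variability (SD) linearly depending on the individual baseline", which the section puts at a quarter of baseline plus 0.5. The stated result is that "the number of 120 subjects in total is sufficient to obtain a power greater than .80".

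The data management and analysis plan section then states: "We will conduct five similar general linear analyses". The outcome is the raw evolution score from T0 to T1. The factors are condition, sex and their interaction, and the covariates are AUDIT and the baseline of the outcome. The baseline covariate is justified by regression to the mean, which concerns the mean and not the variance. Condition is dummy-coded; no coding is given for sex. On follow-up tests the section says "We will investigate the simple effects of condition and sex, should their interaction turn out to be significant". All of this is repeated for T0 to T6.

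The article names no transformation, variance model or robust standard error. It gives no share of men and no BD level or SD by sex.

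**The concern.** An ordinary general linear model estimates one residual variance and uses it for everyone. Under the power section's assumption, the residual variance is larger for participants with a high baseline. If one sex has the higher baseline, the pooled variance is too small for that sex and too large for the other. Adjusting for baseline does not repair this.

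Three results depend on that variance: the condition effect within each sex, the interaction test that decides whether those effects are examined, and the overall condition effect in a model that contains the interaction. The third is the trial's main comparison. The risks are a chance finding in the higher-baseline sex, a missed effect in the other, and a main test that may not run at its nominal 5%.

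**Working it through.** **The plan's own figure.** The stated power above 0.80 at 120 was not reproduced. With the stated decreases and SD, and assumed Gamma shapes 1 to 5 and means 10 to 30, the planned model gave 0.26 to 0.40. Even an ideal relative-scale test with SD 0.25 × baseline has SE 0.25 × √(2/60) = 0.0456 at 60 per arm. So z = 0.10/0.0456 = 2.19, and two-sided power is Φ(2.19 − 1.96) = 0.59. That is a separate problem. The model choice does not explain it, and the error rates below do not depend on it.

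**Inputs from the article.** Alpha 0.05 (taken as two-sided), 120 completers, 1:1 allocation, SD(T1 | B) = B/4 + 0.5, entry at BD score above 1, and a 10% decrease applied to both arms for the null case.

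**Assumed, because the article does not give them.** Gamma shape 2; 30% or 50% men; men/women mean BD of 20/20, 21.6/18, 25/18 or 25/15; Normal T1 noise; AUDIT omitted.

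**Step 1: residual variance by sex.** Averaging over baseline with mean m, V = E[(B/4 + 0.5)²] = E[B²]/16 + m/4 + 0.25. For Gamma shape 2, E[B²] = 1.5m² (entry cut ignored here).
- m = 25: 58.59 + 6.25 + 0.25 = 65.09
- m = 21.6: 43.74 + 5.40 + 0.25 = 49.39
- m = 18: 30.38 + 4.50 + 0.25 = 35.13
- m = 15: 21.09 + 3.75 + 0.25 = 25.09

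**Step 2: one case in full (25/18, 30% men, so 36 men and 84 women).** Pooled variance = 0.3 × 65.09 + 0.7 × 35.13 = 44.12. If R is the true variance divided by the variance the model uses, the rejection rate is about 2[1 − Φ(1.96/√R)].
- Men: R = 65.09/44.12 = 1.48, giving 10.7%.
- Women: R = 35.13/44.12 = 0.80, giving 2.8%.
- Interaction: the true variance is proportional to 65.09/36 + 35.13/84 = 2.226; the model uses 44.12 × (1/36 + 1/84) = 1.751. R = 1.27, giving 8.2%.
- Overall condition effect, sex effect-coded: the plain average of the two sex-specific effects, so R is again 1.27, giving 8.2%.

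**Step 3: all cases with 30% men, no arm difference.** Each cell gives the approximation from step 2, then the simulated rate (2,500 or 6,000 trials per run; a range where several runs were made).

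| Means, men/women | Men | Women | Interaction | Overall |
|---|---|---|---|---|
| 20/20 | 5.0%; 5.1% | 5.0%; 4.7% | 5.0%; 5.1% | 5.0%; about 5% |
| 21.6/18 | 8.0%; 7.9% | 3.8%; about 4% | 6.7%; about 6–7% | 6.7%; about 7% |
| 25/18 | 10.7%; 8.9–10.6% | 2.8%; 2.8–3.6% | 8.2%; 6.8–8.4% | 8.2%; 7.9–8.5% |
| 25/15 | 13.9%; 12.8–13.4% | 1.7%; 1.6–2.4% | 10.1%; 9.4–9.6% | 10.1%; 9.8–10.0% |

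**Step 4: 50% men.** The true variance is (V_men + V_women)/60, and the model uses [(V_men + V_women)/2] × (2/60), which is the same. So R = 1, and the interaction and overall tests stay near 5%. Men still reject in 7.7–10.0% at 25/18 and 25/15.

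**Step 5: the planned gate.** Simple effects are examined only after a significant interaction. With 30% men, a significant interaction plus a significant simple effect occurred in 3.3% with equal baselines, 6.3% at 25/18 and 8.0% at 25/15. Counting only a significant effect in men, the joint rate was 4.1% at 21.6/18, and 3.0–4.2% with 50% men.

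**Step 6: HC3.** With the same model and HC3 standard errors, at 25/18 and 25/15 with 30% men, the four tests rejected in 4.0–4.9%. In the planned analysis at 120 completers, HC3 lowered power for the overall test by 0.7 to 2.7 points (for example 0.327 to 0.310).

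**The case against.** **Size.** A reader might infer that the protocol's own assumptions imply rejection at about 2.5 times alpha. They do not: the inflation needs a baseline gap between the sexes and a sex mix, and the article gives neither. With equal baselines there is no inflation. Nor is 2.5 an upper limit; at an assumed baseline ratio of 2 the men's rate reached 11–20%. The lower-baseline sex is tested conservatively, so it is also wrong to say that sex-specific tests in general reject too often.

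**The gate.** Ungated sex-specific rates overstate what the plan would report. This stands: the gated rate is about 3–8%.

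**The interaction on the points scale.** If the programme lowers BD by the same percentage in both sexes, the interaction is significant in about 9–12% at 25/18 and 25/15. A reader might call these false positives. But the plan defines the effect as added evolution in points, and equal percentages from unequal baselines are unequal in points. For the planned question that difference is real.

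**Replacing the model.** A ratio-scale model would gain about 2–13 points of power under these assumptions, but it changes what is estimated. Percentages in a power simulation do not oblige the analysis to use a ratio.

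**The unseen SAP.** It may already specify robust errors. That is possible. The point rests on what the article states: an ordinary linear model that conflicts with the article's own variance assumption.

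One reassurance fails. The overall test does keep its alpha in a model without the interaction, but the planned model contains it. If sex is dummy-coded instead, the condition coefficient is itself a single-sex test.

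**Conclusion.** The point holds in a limited, conditional form. The article assumes an SD that rises with baseline and then fixes a model whose standard errors ignore it. Whenever the sexes differ in baseline BD, the sex-specific standard errors are wrong; if the sexes are also unequal in number, so are those of the interaction and the overall condition test. Under the assumed inputs (120 completers, shape 2, 30% men, means 21.6/18 to 25/15) the error rates are about 8–13% in the higher-baseline sex, 2–4% in the other, 6–10% for the interaction and 7–10% for the overall test. They are about 5% throughout when baselines are equal.

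Randomisation keeps the mean difference in points unbiased; the fault lies in standard errors, p-values and intervals. This is a worthwhile, cheap improvement and not a fatal flaw.

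**What to change.** In the data management and analysis plan section, keep the raw evolution score and all planned terms. Add that the BD model uses heteroscedasticity-consistent (HC3) standard errors for the condition effect, the condition-by-sex interaction and the simple effects, at T1 and T6. Do the same for weekly alcohol consumption, where spread is also likely to grow with level (a judgement; it was not simulated). State the coding of sex, so that it is clear which condition effect is the main test.

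Optionally, add a sensitivity analysis of follow-up BD with a log link and variance proportional to the squared mean, reported as a ratio with its 95% CI. This matches the percentage scale of the power section without replacing the planned effect.

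The cost is a sentence of SAP wording and a few lines of R, with no new data or participants. HC3 is slightly conservative (about 4–5% in place of 5%) and gives up roughly 1–3 points of nominal power.
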